## Abstract

**Introduction:**

Previous studies demonstrated that wedge resection is sufficient for ground glass-dominant lung adenocarcinoma (LUAD) with tumour diameter ≤2 cm, however, the optimal surgical type for ground glass-dominant LUAD with tumour diameter of 2–3 cm remains unclear. The purpose of this trial is to investigate the safety and efficacy of segmentectomy for ground glass-dominant invasive LUAD with tumour size of 2–3 cm.

**Methods and analysis:**

We initiated a phase III trial to investigate whether segmentectomy is suitable for ground glass-dominant invasive LUAD with tumour size of 2–3 cm. This trial plans to enrol 307 patients from multiple institutions including four general hospitals and two specialty cancer hospitals over a period of 5 years. The primary endpoint is 5 year disease-free survival. Secondary endpoints are lung function, 5 year overall survival, the site of tumour recurrence and metastasis, segmentectomy completion rate, radical segmentectomy (R0 resection) completion rate and surgery-related complications.

**Ethics and dissemination:**

This trial has been approved by the Ethics Committee of Fudan University Shanghai Cancer Centre (reference 2212267-18) and by the institutional review boards of each participating centre. Written informed consent is required from all participants. The study results will be published in a peer-reviewed international journal.

**Trial registration number:**

NCT05717803.

Strengths and limitations of this studyThe trial is conducted in multiple centres, increasing the generalisability of the results.Both intraoperative frozen sections and postoperative paraffin sections will be evaluated by two experienced pathologists, making the pathologic diagnosis reliable.A key limitation of the trial is lack of a comparator group; considering the indolent nature and excellent prognosis of ground glass-dominant lung adenocarcinoma, lobectomy might be too invasive, so a control-arm of lobectomy is not set.

## Introduction

Lung cancer is the most commonly diagnosed malignancy in men and the leading cause of cancer-associated mortality in both men and women.^1^ Since the national lung screening trial demonstrated that screening with low-dose CT (LDCT) could increase the detection of lung cancer, and reduce the risk of mortality from lung cancer, LDCT is widely used in the screening for lung cancer.^2^ LDCT screening leads to a dramatic increase in the detection of small-sized lung nodules, especially ground-glass opacity (GGO).^3^ The shift of the spectrum of radiological characteristics challenges lobectomy as the ‘gold standard’ of surgical treatment for early-stage lung cancer, which was established in the 1990s by the Lung Cancer Study Group trial.^4^

From 2002 to 2004, the JCOG0201 trial included patients with clinical T1N0M0 (≤3 cm in tumour diameter) peripheral lung cancer, and defined radiological non-invasive lung adenocarcinoma (LUAD) as tumour size ≤2 cm with consolidation-to-tumour ratio (CTR) ≤0.25.^5^ Afterward, the JCOG1211 trial found that the 5 year recurrence-free survival (RFS) of patients undergoing segmentectomy for the ‘radiologically invasive’ tumours (tumour diameter ≤2 cm with CTR between 0.25 and 0.50, or tumour diameter between 2 cm and 3 cm with CTR≤0.50) is 98.0%, exceeding the 87% of the preset threshold.^6^ However, this trial was criticised on the basis that about half of the included patients were pathologically confirmed as adenocarcinoma in situ (AIS) and microinvasive adenocarcinoma (MIA). For these patients (AIS/MIA), wedge resection is sufficient, and segmentectomy may be unnecessary. Additionally, this also limits the statistical power to demonstrate the efficacy of pathologically invasive LUAD. Recently, our team performed a retrospective study and found that wedge resection for peripheral invasive LUAD with tumour diameter ≤2 cm and CTR≤0.5 could lead to excellent long-term survival.^7^

This single-arm, multicentre, phase III trial (ECTOP1012) aims to investigate whether segmentectomy is suitable for ground glass-dominant invasive lung cancer with tumour size of 2–3 cm.

## Methods and analysis

### Study design

ECTOP1012 is a single-arm, multicentre, confirmatory phase III trial to evaluate the safety and efficacy of segmentectomy for ground glass-dominant invasive lung cancer with size of 2–3 cm. Four general hospitals and two specialty cancer hospitals will participate in this trial. As the prognosis of these patients is fairly excellent, a large sample size would be required if a randomised controlled trial (RCT) is to be performed, so this study is designed as a single-arm confirmatory trial. The tumour size should be between 2 and 3 cm, and the CTR should not be greater than 0.5 on preoperative high-resolution CT. The surgical procedure for included patients is segmentectomy, which includes single-segment resection, combined segment resection, trisegmentectomy and basal segment resection. Tumours located in the right middle lobe are excluded in this trial (figure 1).

**Figure 1 F1:**
[figure not shown]
Study flowchart. CTR, consolidation-to-tumour ratio.

The trial started in February 2023; the estimated primary completion date is December 2028 and the estimated study completion date is December 2029. We used the Standard Protocol Items: Recommendations for Interventional Trials (SPIRIT) checklist when preparing this report.^8^

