### Endpoints

The primary endpoint is 5 year disease-free survival (5 year DFS). DFS events are defined as tumour recurrence due to lung cancer or death from any cause. Alive patients without recurrence at the last follow-up are defined as censored.

The secondary endpoints are lung function, 5 year overall survival, the site of tumour recurrence and metastasis, segmentectomy completion rate, radical segmentectomy (R0 resection) completion rate and surgery-related complications.

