#### Calculation of sample size

According to the results of previous studies, for patients undergoing lobectomy with tumour sizes of 2–3 cm, CTR≤0.5 and the 5 year DFS was 97.0% after surgery.^13^ In this trial, we assumed that the expected 5 year DFS for these patients undergoing segmentectomy is 95%. A sample size of 292 achieves 90.193% power to detect a non-inferiority proportion of 90% (5% as the non-inferior boundary) using a one-sided exact test with a target significance level of 0.0250. Considering a possible dropout rate of 5%, a total of 307 cases need to be included in this trial.

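### Primary completion in December 2028 falls before most patients can reach 5 years, so the 5-year DFS test and its 90% power do not fit the stated timetable

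*Protocol article*

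**What the plan says.** Four statements in the Protocol article bear on this.

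- **Start and end dates** (Study design, below Figure 1): on the start, "The trial started in February 2023". On the end, it says that "the estimated primary completion date is December 2028 and the estimated study completion date is December 2029".
- **Accrual** (Abstract, Methods and analysis): "This trial plans to enrol 307 patients from multiple institutions including four general hospitals and two specialty cancer hospitals over a period of 5 years". No other accrual period, and no accrual rate, is given anywhere in the article.
- **Endpoint** (Endpoints): "The primary endpoint is 5 year disease-free survival (5 year DFS"). On censoring it adds: "Alive patients without recurrence at the last follow-up are defined as censored".
- **Sample size** (Calculation of sample size): "we assumed that the expected 5 year DFS for these patients undergoing segmentectomy is 95" per cent, and "A sample size of 292 achieves 90.193% power to detect a non-inferiority proportion of 90" per cent. The test is a one-sided exact test at 0.025. Adding 5% for dropout gives 307.

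The section on analysis sets also prescribes last observation carried forward (LOCF) for missing data in the full analysis set, which is the primary set.

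**The concern.** An exact test of a proportion needs a known 5-year status for each of the 292 patients. For a patient without an event, that means 60 months of follow-up. Sixty months of accrual plus 60 months of follow-up is 120 months, but the timetable allows about 70 months to primary completion and about 82 to study completion.

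If the confirmatory test were run on the stated date, most patients would have an unknown 5-year status. The analysis would then have to do one of three things:

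- use only the few early patients;
- rely on a Kaplan–Meier estimate with few patients at risk at 5 years;
- count patients not yet at 5 years as disease-free.

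The first two lose power, and the third biases the result towards success. The article describes the trial as confirmatory phase III, so the date of the primary test matters. The secondary endpoint of 5-year overall survival has the same problem.

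**Working it through.** **Inputs from the article.** Start February 2023 (month 0); primary completion December 2028 (months 70–71, midpoint 70.5); study completion December 2029 (months 82–83, midpoint 82.5); 307 patients over 60 months; null proportion 0.90, expected proportion 0.95; one-sided exact test at 0.025; 292 evaluable.

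**Assumptions, not in the article.** Uniform accrual throughout. Constant hazard for the Kaplan–Meier and LOCF figures.

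**1. The stated power reproduces.** The smallest r with P(X ≥ r | n = 292, p = 0.90) ≤ 0.025 is r = 273, with actual alpha 0.0242. Then P(X ≥ 273 | p = 0.95) = 0.9019, which matches 90.193%. The sample-size calculation is not the defect.

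**2. Calendar.** The last patient enters at month 60 (February 2028) and reaches 5 years at month 120 (February 2033). That is 120 − 70 = 50 months after the stated primary completion and 120 − 82 = 38 months after study completion. For every patient to have 60 months by December 2028, enrolment must end by month 70 − 60 = 10 (December 2023). For December 2029 it must end by month 82 − 60 = 22 (December 2024).

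**3. Patients who can have reached 5 years.** Share = (cut-off month − 60)/60.

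- December 2028: 10.5/60 = 17.5%, and 0.175 × 307 ≈ 54 (51 at month 70, 56 at month 71).
- December 2029: 22.5/60 = 37.5%, and 0.375 × 307 ≈ 115 (113 at month 82, 118 at month 83).

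**4. Exact test on those patients only, true DFS 95%.**

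| Cut-off | n | Successes required | Power |
|---|---|---|---|
| December 2028 | 51 | 51 | 7% |
| December 2028 | 53 | 53 | 7% |
| December 2028 | 54 | 53 | 24% |
| December 2028 | 56 | 55 | 22% |
| December 2029 | 113 | 109 | 33% |
| December 2029 | 114 | 109 | 49% |
| December 2029 | 118 | 113 | 46% |

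The jumps come from the discreteness of the test, so the range is more informative than any single value.

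**5. Kaplan–Meier estimate at 60 months using censored follow-up.** Simulation with 307 patients; success if the lower 97.5% bound exceeds 90%.

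| Cut-off | Power, log-log bound | Power, plain bound |
|---|---|---|
| December 2028 | about 58% | about 76% |
| December 2029 | about 75% | about 88% |
| Full 5-year follow-up | about 91% | about 94% |

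At a true 90%, the plain bound succeeds falsely about 6% of the time in December 2028 and about 5% in December 2029, instead of 2.5%, so part of its apparent power is inflated error. With 292 patients the log-log figures are about 56%, 72% and 85%. In December 2028 about 46 of 292 patients remain at risk at 5 years.

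**6. If LOCF carried patients not yet at 5 years forward as disease-free.** Take a true 5-year DFS of 90%, so λ = −ln(0.90)/60 = 0.001756 per month. At month 70.5 a share of 0.175 has full follow-up. The remaining 0.825 have follow-up spread evenly from 10.5 to 60 months.

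- Mean event-free proportion of that remainder: (e^(−10.5λ) − 0.90)/(49.5λ) = (0.9817 − 0.90)/0.0869 ≈ 0.940.
- Apparent DFS: 0.175 × 0.90 + 0.825 × 0.940 ≈ 93.3%.
- The exact test on 307 succeeds with 287 or more. P(X ≥ 287 | n = 307, p = 0.933) ≈ 51%, where at most 2.5% is intended.
- At month 82.5 the same steps give an apparent DFS of about 91.9% and false success of about 18%.

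**7. Shorter accrual.** Share of patients with 5 years in December 2028 (month 70), and exact-test power on that share of 292:

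| Accrual (months) | Share | Power |
|---|---|---|
| 60 | 17% | 8% |
| 48 | 21% | 18% |
| 36 | 28% | 22% |
| 24 | 42% | 43% |
| 12 | 83% | 84% |
| 10 | 100% | 90% |

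Most patients fall short for any uniform accrual longer than about 20 months, since 10/20 = 50%.

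**The case against.** **The abstract may be what is wrong.** The 5-year accrual period appears only there. About 10 months of enrolment plus 60 months of follow-up would end in December 2028 as printed. This possibility stands, and the article should say which was meant. But the sentence speaks of enrolling patients over that period, and on the other reading all 307 would have to enter within about 10 months. One statement has to change either way.

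**Kaplan–Meier can use censored patients.** The endpoint definition provides for censoring, so not every patient strictly needs 60 months. This partly stands. With a December 2028 cut-off and 307 patients, Kaplan–Meier power (log-log to plain bound) is about 91–94% for 12-month accrual, 85–93% for 24 months and 77–87% for 36 months. A moderately longer accrual would therefore not be fatal. It is still not the test that the sample size was built on, and under the stated 60 months the loss remains large.

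**LOCF may not apply.** The text most naturally concerns data missing after dropout, and patients not yet at 5 years are covered by the censoring rule. That is fair. The 51% figure is conditional; the article neither prescribes nor excludes that use, and the conclusion does not depend on it.

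**The dates are estimates.** They are labelled so, and nothing says that the test will be run on that day regardless. But a gap of about four years for the last patient is beyond ordinary uncertainty in a forecast.

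**Conclusion.** The concern holds. The start date, 5-year accrual, 5-year endpoint and completion dates are all stated and are mutually incompatible, and nothing in the article reconciles them. This part rests on calendar arithmetic alone.

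The size of the effect rests on uniform accrual and, for the survival figures, a constant hazard. About 83% of patients would fall short of 5 years in December 2028 and about 63% in December 2029. Every analysis examined without carrying patients forward loses power: severely for the exact test on complete patients, and by roughly 20 to 30 percentage points for Kaplan–Meier in December 2028. The endpoint and the 292-patient calculation are sound in themselves, but the stated 90% power is not available on the stated dates. This must be corrected before the timetable is used to schedule the confirmatory test.

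**What to change.** State the accrual period, the follow-up per patient and the completion dates so that they agree across the abstract, Study design, Endpoints and Calculation of sample size. Define the primary analysis as taking place when the last enrolled patient has completed 5 years of follow-up. With 5-year accrual that is about early 2033. If the 5 years in the abstract meant follow-up, say so and give the true accrual period; the same rule then sets the date.

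State that no confirmatory test of 5-year DFS will be made before that point, and that any 2028 or 2029 report is descriptive. Apply the same timing to 5-year overall survival. State also that patients not yet at 5 years are censored and never carried forward as disease-free.

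The cost is an amendment of the dates, a registry update and, under 5-year accrual, a confirmatory result about four years later than the article implies. No extra patients are needed, and the endpoint already implies 5 years of follow-up for each patient.

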### Objectives

The primary objective of ECTOP1012 is to assess the efficacy of segmentectomy for ground glass-dominant invasive lung cancer with size of 2–3 cm.

The secondary objectives include:

Surgical safety of segmentectomy for ground glass-dominant invasive lung cancer with size of 2–3 cm.Loss of lung function after segmentectomy.Tumour recurrence rate after segmentectomy.

### Endpoints

The primary endpoint is 5 year disease-free survival (5 year DFS). DFS events are defined as tumour recurrence due to lung cancer or death from any cause. Alive patients without recurrence at the last follow-up are defined as censored.

The secondary endpoints are lung function, 5 year overall survival, the site of tumour recurrence and metastasis, segmentectomy completion rate, radical segmentectomy (R0 resection) completion rate and surgery-related complications.

### Eligibility criteria

#### Inclusion criteria

All enrolled patients should meet the following criteria:

Written informed consent.18–80 years old (including cut-off value) at the time of signing the informed consent.Eastern Cooperative Oncology Group (ECOG) score of 0 or 1.No prior lung cancer surgery.Invasive LUAD confirmed by intraoperative or postoperative pathological evaluation.A single pulmonary nodule with a predominantly ground-glass component or pure ground-glass on CT, or multiple pulmonary nodules but the main lesion is the above-mentioned nodule.The CTR of the nodule ranges from 0 to 0.5, and the total size is between 2 and 3 cm.No evidence of nodal or distant metastasis.The tumour is evaluated to be completely removed via segmentectomy by thoracic surgeon.No prior radiotherapy or chemotherapy.

Exclusion criteria

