#### Exclusion criteria

Patients are excluded if they meet any of the following criteria:

1.CTR is not between 0 and 0.5 or the total nodule size is not between 2 and 3 cm.

2.The lesion cannot be completely surgically removed by segmentectomy.3.Lung malignancies other than lung adenocarcinoma confirmed by cytological or histopathological evaluation.4.Prior lung cancer surgery.5.Non-treatment-naïve patients.

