#### Intraoperative frozen pathological evaluation criteria

All primary tumours are sent to the pathology room for frozen section diagnosis immediately after resection. Frozen pathology is taken from the maximum diameter of the tumour. Diagnosis is based on the 2015 WHO classification criteria.^12^ Lesions diagnosed as invasive lung adenocarcinoma/non-small cell lung cancer by intraoperative frozen are included in this study.

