#### Postoperative pathological evaluation criteria

The postoperative pathological diagnosis of the tumour using paraffin sections is based on the 2015 version of the WHO classification criteria, and patients with lung adenocarcinoma are included in this study. All pathology reports are evaluated by two experienced pathologists.

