### Statistical analysis

#### Analysis sets

Full analysis set (FAS): determined according to the intention-to-treat principle, including all enrolled cases who have undergone segmentectomy.

Per-protocol set (PPS): subset of the FAS population, including all cases that meet the protocol and have completed case report form.

In this trial, FAS analysis is used for baseline data and validity analysis. The main efficacy indicators are will be analysed in the FAS and PPS data sets. However, the analyses of the FAS data set are considered primary. When analyses of the FAS and PPS reach consistent conclusions, confidence in the conclusions can be increased. For the FAS data set, the missing data after the fall are estimated using the last observation carried forward method.

The laboratory examination data and adverse events will be analysed using SPSS and Stata software.

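### A tumour called invasive on frozen section but AIS or MIA on paraffin stays eligible and counts in the primary DFS analysis of invasive disease

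*Protocol article*

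**What the plan says.** The primary objective (Protocol article, Objectives) is to "assess the efficacy of segmentectomy for ground glass-dominant invasive lung cancer with size of 2–3 cm". Three sections then say which pathology counts:

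- Inclusion criteria: "Invasive LUAD confirmed by intraoperative or postoperative pathological evaluation".
- Intraoperative frozen pathological evaluation criteria: "Lesions diagnosed as invasive lung adenocarcinoma/non-small cell lung cancer by intraoperative frozen are included in this study".
- Postoperative pathological evaluation criteria, on paraffin sections: "patients with lung adenocarcinoma are included in this study".

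The one exclusion based on histology is "Lung malignancies other than lung adenocarcinoma confirmed by cytological or histopathological evaluation". The primary analysis uses the full analysis set (FAS), "including all enrolled cases who have undergone segmentectomy". The per-protocol set (PPS) is the part of the FAS that meets the protocol and has a completed case report form.

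The Introduction criticises an earlier segmentectomy trial because roughly half of its patients had AIS or MIA, and adds that "this also limits the statistical power to demonstrate the efficacy of pathologically invasive LUAD".

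**The concern.** The trial has one arm. Success depends on a single pooled proportion against a fixed 90% threshold, so case mix feeds straight into the result. If AIS/MIA patients have better DFS than invasive patients, each one included lifts the pooled figure and makes it easier for an invasive population at the threshold to pass. The Introduction names dilution by AIS/MIA as the weakness of the earlier evidence. The entry rule should not let it back in, even on a smaller scale, when the deciding information (the paraffin diagnosis) is collected anyway.

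**Working it through.** **Step 1. Follow each combination of readings through the stated rules.**

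| Frozen | Paraffin | Outcome under the text |
|---|---|---|
| invasive | invasive adenocarcinoma | eligible, as intended |
| AIS/MIA | AIS/MIA | not eligible: the inclusion criterion needs invasive disease on at least one examination |
| AIS/MIA | invasive adenocarcinoma | eligible through the postoperative limb |
| invasive (LUAD/NSCLC) | malignancy other than adenocarcinoma | excluded by the histology exclusion |
| invasive | AIS/MIA | eligible: the intraoperative limb is met, and the histology exclusion does not apply |

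Only the last row is a gap. Nothing later closes it. Withdrawal for enrolment error applies to patients who do not meet the criteria, and this patient does. The FAS takes all enrolled patients who had segmentectomy. The PPS takes those who meet the protocol, which this patient also does, so comparing FAS with PPS cannot reveal the problem.

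**Step 2. Reproduce the plan's figure.** Inputs from Calculation of sample size: n = 292, threshold 0.90, expected DFS 0.95, one-sided exact test at 0.025. The smallest r with P(X ≥ r | 292, 0.90) ≤ 0.025 is r = 273, that is, at most 19 events.

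- Attained type I error: P(X ≥ 273 | 292, 0.90) = 0.0242.
- Power: P(X ≥ 273 | 292, 0.95) = 0.90193, which matches the stated 90.193%.

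**Step 3. Add discordant cases.** Let f be the AIS/MIA share on paraffin and q the 5-year DFS in AIS/MIA. Both are assumptions, because the protocol gives neither. With invasive DFS at 90%:

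pooled DFS = (1 − f) × 0.90 + f × q; false success = P(X ≥ 273 | 292, pooled DFS).

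Example: f = 0.05, q = 1.00 gives 0.95 × 0.90 + 0.05 = 0.905, and P = 0.0446.

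| f | pooled DFS, q = 98% | false success | pooled DFS, q = 100% | false success |
|---|---|---|---|---|
| 0 | 90.00% | 2.4% | 90.0% | 2.4% |
| 1% | 90.08% | 2.7% | 90.1% | 2.8% |
| 3% | 90.24% | 3.3% | 90.3% | 3.5% |
| 5% | 90.40% | 4.0% | 90.5% | 4.5% |
| 10% | 90.80% | 6.3% | 91.0% | 7.8% |

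If AIS/MIA DFS were only 95%, because deaths from any cause count as events, false success would be 3.3% at f = 5% and 4.5% at f = 10%.

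**Step 4. Power if only confirmed invasive cases count and enrolment is unchanged.** The cut-off is recomputed for each n.

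| Lost from 292 | Confirmed n | Cut-off | Power at 95% |
|---|---|---|---|
| 5% | 277 | 260 | 84.3% |
| 10% | 263 | 247 | 83.0% |

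Part of this fall comes from the discreteness of the exact test. At n = 291 the cut-off is still 273, and power is already 85.6%.

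**The case against.** Four points can be made against the concern.

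*The postoperative section is not a way in.* A reader might infer from its wording that any adenocarcinoma on paraffin qualifies, so that AIS/MIA may enter freely. The text does not support this. All enrolled patients must meet the inclusion criteria, which require invasive disease on one examination, and the frozen-section rule also says invasive. This stands, and it limits the concern to the discordant case.

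*It does not recreate the earlier trial's problem.* A reader might infer contamination near that trial's half. Here every patient needs an invasive reading, and two experienced pathologists evaluate both frozen and paraffin sections. The share should be far lower. This stands too.

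*A 90% invasive DFS may be remote.* The protocol cites 97.0% 5-year DFS after lobectomy and 98.0% 5-year recurrence-free survival in the earlier segmentectomy trial. If half of the latter's patients had 100%, the other half would have (0.98 − 0.5 × 1.00) / 0.5 = 96%. This is rough, since the endpoint differs and some of those tumours were 2 cm or smaller. It makes a false success less likely in practice, but the error rate of the test is still judged at its own threshold.

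*The article is condensed.* Handling of discordant readings may be in the full protocol, and a subset analysis in the analysis plan. That would excuse silence. Here the article states a rule, and the rule admits the discordant patient.

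**Conclusion.** The gap is real but narrow: tumours read as invasive on frozen section and as AIS/MIA on paraffin stay eligible and count in both analysis sets, contrary to the stated objective. The direction of bias is upward, provided AIS/MIA patients have better DFS than invasive patients. Its size is unknown. At a 1–3% share, false success moves only from 2.4% to 2.7–3.5%; it reaches 6.3–7.8% at 10%. These are scenarios with a true invasive DFS of 90% and AIS/MIA DFS of 98–100%, not estimates. The case for change is that the remedy is cheap and uses information already collected; the documents do not show that the trial is likely to succeed wrongly.

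**What to change.** Align the inclusion criteria and the two pathology sections so that the final paraffin diagnosis of invasive adenocarcinoma defines the primary DFS analysis population, with the frozen-section reading provisional. Add the word invasive to the postoperative rule, and bring the frozen-section reference to non-small cell lung cancer into line with the adenocarcinoma criterion. Report patients with invasive frozen section but AIS/MIA on paraffin separately, and give the all-segmentectomy FAS result as a sensitivity analysis. The paraffin diagnosis comes from the resected specimen, before DFS follow-up, so the restriction need not select on outcome.

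The paraffin review is already planned, so the cost is wording and some power. Discordant patients no longer count towards the 292, and the stated 90.193% should be restated for the confirmed number (Step 4). Keeping 292 confirmed cases with the planned 5% dropout would instead need 292 / (0.95 × 0.95) ≈ 324 enrolled at 5% discordance, or 292 / (0.90 × 0.95) ≈ 342 at 10%, against the planned 307. With discordance of 1–3%, the loss is about 3 to 9 of the 292 patients.
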